### Data handling, analysis and result reporting

At study entry, baseline demographics, medical and obstetric history will be collected. Antenatal data pertaining to the secondary outcomes will be collected throughout gestation including blood pressure data, investigations undertaken and any contact with the healthcare system. For the interventional arm, the M♡THer application will collect blood pressure data, symptom checklists and weight. At delivery, relevant data will be collected from the electronic medical record for the assessment of foetal outcomes such as gestational age at birth, birth weight, Apgar scores, and high-level neonatal care admission. For maternal outcomes, data will be collected from the electronic medical record on mode of delivery, antihypertensive medication use and adverse outcomes. Standardised online case report forms developed by investigators through REDCap™ will be used, and data will be stored on password-protected cloud drives located behind a university firewall, available only to investigators.

Data analyses will primarily be carried out according to the intention-to-treat principle but we will also perform per protocol analyses excluding participants in whom there is a clear deviation of the intended care as prescribed by the protocol in either the control group or the remote monitoring group. We will undertake both analyses with and without imputed data. We anticipate that some patients within the conservative care arm will undertake home blood pressure monitoring using their own devices. In such cases, we will ensure that during consultations, changes to medications will not be made based on home blood pressure readings provided by the patient. However, if there are clinical concerns, we would advise participants in the conventional arm to be assessed in the local birthing unit as is current standard of care. The case reporting form will take note of patients who are part of the conservative care arm that own blood pressure machines, and this will be adjusted for in a sensitivity analysis as a potential confounder.

Results will be reported according to Consolidated Standards of Reporting Trials (CONSORT) guidelines, using the extension for non-inferiority trials [44].

The dichotomous primary outcome will be analysed using a generalised linear model (with binomial distribution and log link), adjusting for minimisation variables, chronic hypertension and aspirin use. Treatment effects will be expressed as adjusted risk ratios with 95% CIs. The secondary outcomes that are binary will be analysed using the same methods described for the primary outcomes, with corresponding 95% CIs. For those secondary outcomes that are continuous, data that is normally distributed will be analysed with parametric tests and non-normally distributed data will be analysed with non-parametric tests. Significance will be set at 0.05 and adjustments for multiple comparisons will be made where comparing several groups.

Subgroup analyses will be undertaken on (i) variables used in the minimisation algorithm (i.e. hypertension type [chronic or gestational hypertension] and LDA use); and (ii) other variables of prognostic significance pre-specified as ethnicity, body mass index, prior severe hypertension in the index pregnancy, antihypertensive therapy at randomisation, gestational diabetes mellitus at randomisation, and smoking status at randomisation. Subgroup analyses will be limited to the primary outcome. Results will be presented as adjusted risk ratios with 95% confidence intervals. The results of subgroup analyses will be treated with caution and will be used for the purposes of hypothesis generation only.

Participants with missing primary outcome data will not be included in the primary analysis in the first instance. This presents a risk of bias, and sensitivity analyses will be undertaken to assess the possible impact of the risk. Sensitivity analyses will also be undertaken for the women who were randomised to the conventional care arm, who had a remote blood pressure monitor at home. A post-hoc analysis will be undertaken for aspirin compliance as a modifier based on PFA-100 levels.

Comparison of questionnaires will be made for each time point.

A’within trial’ economic evaluation will be conducted alongside the trial from a health sector perspective, and extending to patient and carer costs. This will combine three forms of complimentary economic analysis in a comprehensive approach.

First, a cost effectiveness analysis (CEA) will compare remote monitoring against usual care and estimate the incremental cost per change in the primary composite adverse patient outcome. In the non-inferiority approach, it is hypothesized that remote monitoring will reduce costs with no significant change in outcomes. Costing will consider the difference in implementing the model of care between trial arms. In usual care, this will include the time cost of each specialist visit, and the time and travel cost of patients (and carers, if relevant). In remote monitoring, this will include the cost of each unit of equipment, development of training, and time in undertaking educational training (professional and patient), specialist time to review BP readings, and patient visit to specialists (similar to usual care, describe above). MBS will be used to cost professional time and average hourly wage rates used to value for patient/carer time. For both trial arms, health care utilisation will be compared and costed using reference costs from the Independent Hospital Pricing Authority (IHPA).

Secondly, a cost-utility analysis (CUA) will compare trial arms and estimate the incremental cost per change in ‘health utility’ as the outcome measure, replacing the composite adverse outcome. Health utility is an indexed measure of (preference-weighted) patient quality of life, will be measured by the EQ5D and used to generate quality-adjusted life years (QALYs). QALYs will then be converted to dollar values by multiplying each QALY by $50,000. By combining monetized QALYs and costs a measure of ‘net benefit’ is generated where a positive value indicates value for money.

Thirdly, a value of information (VOI) analysis will then estimate statistical uncertainty whether remote monitoring is cost-effective. In a Bayesian analysis, an estimate of the economic value of undertaking further research will be made to reduce parameter uncertainty (cost and outcomes) and increase confidence that remote monitoring is cost-effective. The VOI will then extend to investigate subgroup heterogeneity and to explore whether remote monitoring is relatively more (or less) cost-effective in particular groups, to inform whether further research can best focus on subgroups where uncertainty is greatest.

All adverse events experienced by the trial participant, from randomisation until 3 months postpartum, will be collected and considered for causal links to the study. Serious adverse events not pre-specified as protocol-exempt will be reported to the data monitoring committee. The data monitoring committee will consist of an Obstetrician and Obstetric Medicine physician, independent from the sponsor and competing interests. The data monitoring committee and ethics committee will meet to review trial conduct if adverse events arise during the trial. The Trial Management Group (TMG) will include those individuals responsible for the day-to-day management of the trial — the coordinating principal investigator (CPI) and the site lead investigators and site allocated research midwife. The role of the group is to monitor all aspects of the conduct and progress of the trial, ensure that the protocol is adhered to and take appropriate action to safeguard participants and the quality of the trial itself. The TMG will meet 3-monthly. No problems directly related to the intervention that are detrimental to the participants are anticipated, and therefore no interim analyses and formal stopping guidelines have been outlined.

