#### Intervention arm: remote monitoring of BP

Prior to the start of the study, we will provide training of the remote monitoring strategy at each site to ensure familiarity with the technological aspects. A research midwife at each centre will be trained how to register, train and enrol new participants on the novel platform (consisting of an automated blood pressure device connected via Bluetooth to a smartphone application) after randomisation. As set in the research protocol, responsibilities of the clinicians will include review of uploaded parameters, management after reviewing new results and telephone contact with the pregnant women at home.

Women randomised to remote monitoring will be provided with an automated BP machine validated for use in pregnancy and preeclampsia (iHealth Track), which uploads blood pressure readings to a smartphone application (M♡THer). They will be educated on its use at their first visit by a research midwife or investigator. The smartphone application and innovative platform (M♡THer), was developed by the Commonwealth Scientific and Industrial Research Organisation (CSIRO) Australian e-Health Research Centre (AEHRC) and has been found to be feasible in supporting remote monitoring of women with diagnosis of gestational diabetes [39]. For this trial the application has been customised to focus on BP monitoring.

Education will be provided through a standardised video created by the trial team in addition to a patient information sheet with telephone contact numbers for technical or health-related questions. Participants will have any questions about the intervention answered.

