**Fig. 2 Fig2:**
[figure not shown]
Participant timeline

Increasingly, women are utilising home blood pressure monitoring during pregnancy. However, the interpretation of these blood pressure readings is left to the patient, without clear guidance on normal and abnormal values in pregnancy. Our trial aims to evaluate the effectiveness and safety of remote blood pressure monitoring. Remote blood pressure monitoring in this trial refers to not only home blood pressure monitoring, but also a system whereby readings are transmitted to clinicians for review, in addition to immediate interpretation for patients about normal and abnormal values in the context of pregnancy, founded on evidence-based guidelines. This allows for proactive, rather than reactive care.

Therefore, as a pragmatic trial, women within the control arm may still undertake home blood pressure monitoring but are not encouraged to do so. This would fall within the scope of conventional care as defined in the trial protocol. For participants within the usual care arm who undertake home blood pressure monitoring using their own devices, decisions about clinical care will not be made based on home blood pressure readings provided by the patient in between appointments. However, for participants who report hypertension measured at home, usual clinical practice would be followed. Clinicians would validate this through more regular clinical visits, undertaking appropriate investigations and a formal blood pressure assessment in the fetomaternal assessment unit. Participants will also be advised that should they have clinical concerns, they should present to their local birthing unit for assessment.

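### Adjusting for blood pressure machine ownership that appears to be noted only for control women moves the comparison to a self-selected part of the control arm and can bias the sensitivity analysis

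*Protocol article*

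**What the plan says.** In the Protocol article, Data handling, analysis and result reporting, the covariate is defined within one arm: the case report form is to note "patients who are part of the conservative care arm that own blood pressure machines, and this will be adjusted for in a sensitivity analysis". The end of that sentence gives the reason for adjusting: "this will be adjusted for in a sensitivity analysis as a potential confounder". Later in that section, sensitivity analyses are planned for "women who were randomised to the conventional care arm, who had a remote blood pressure monitor at home", so the group is again defined by control-arm membership.

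Two other sections bear on this. Under Intervention arm: remote monitoring of BP, "Women randomised to remote monitoring will be provided with an automated BP machine". Under Control arm: usual care, "women within the control arm may still undertake home blood pressure monitoring but are not encouraged to do so", and the article places such monitoring within conventional care. The primary model is a "generalised linear model (with binomial distribution and log link), adjusting for minimisation variables, chronic hypertension and aspirin use"; machine ownership is not in it.

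**The concern.** A covariate can adjust a treatment comparison only if it is measured in the same way in both arms. Here it separates owners from non-owners among control women, while all remote women carry a single value: 0 if they were not asked, 1 if the supplied machine counts. Its coefficient is then estimated from control women alone, and the treatment coefficient takes one part of the control arm as its reference. Women choose whether to own a machine, so that part is self-selected.

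The label is also wrong. Ownership before randomisation is balanced in expectation and so does not confound the comparison. Ownership acquired after randomisation is a post-randomisation variable. The article does not say at which time ownership is noted.

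What is at stake is how the sensitivity analysis is read. It is the stated check on home monitoring among control women, and it could suggest harm or benefit where there is none.

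**Working it through.** **The plan's own figure.** Sample size gives a risk of 31.1%, a 15-point margin, one-sided α 0.05, power 0.80 and 118 women per arm. Check: (1.645 + 0.842)² × 2 × 0.311 × 0.689 / 0.15² ≈ 6.18 × 19.05 ≈ 117.8, so 118. This figure is reproduced. The article gives no figure for the ownership adjustment.

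**What the adjusted model estimates.** Write log(risk) = a + bT + cO, with T = 1 for remote and O = 1 for owner.

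- O = 0 for all remote women: exp(a) is the risk in control non-owners and exp(a + b) the risk in the whole remote arm. So exp(b) = remote risk / control non-owner risk.
- O = 1 for all remote women: exp(a + c) is the risk in control owners and exp(a + b + c) the risk in the whole remote arm. So exp(b) = remote risk / control owner risk.
- O missing for remote women: a complete-case fit drops the remote arm and no treatment effect can be estimated.

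**Size when there is no true effect.** Inputs: overall risk p = 0.311 (Sample size). Ownership q and the owner to non-owner risk ratio r are assumptions; the article gives neither.

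Non-owner risk = p / (1 − q + qr); owner risk = r × non-owner risk. Hence RR = 1 − q + qr when remote women are coded 0, and RR = (1 − q + qr) / r when they are coded 1.

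For q = 0.4 and r = 1.5: 1 − 0.4 + 0.6 = 1.20. Non-owner risk = 0.311 / 1.20 = 0.259 and owner risk = 0.389. Coded 0: RR 1.20, difference 0.311 − 0.259 = +5.2 points. Coded 1: RR 1.20 / 1.5 = 0.80, difference 0.311 − 0.389 = −7.8 points.

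| r (q = 0.4) | Non-owner risk | Owner risk | Remote coded 0: RR (difference) | Remote coded 1: RR (difference) |
|---|---|---|---|---|
| 0.67 | 0.358 | 0.240 | 0.87 (−4.7 points) | 1.30 (+7.1 points) |
| 1 | 0.311 | 0.311 | 1.00 (0) | 1.00 (0) |
| 1.5 | 0.259 | 0.389 | 1.20 (+5.2 points) | 0.80 (−7.8 points) |
| 2 | 0.222 | 0.444 | 1.40 (+8.9 points) | 0.70 (−13.3 points) |

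Over q = 0.2 to 0.6 and r = 0.67 to 2, coding 0 gives RR 0.80 to 1.60 and coding 1 gives RR 0.60 to 1.39.

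**Simulation.** Log-binomial fits with treatment and ownership only, 118 per arm, q = 0.4, no true effect, 1,500 runs per scenario, nominal 2.5% per direction:

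- r = 1.5: false harm in 8.9% (coded 0); false benefit in 17.8% (coded 1).
- r = 0.67: false benefit in 10.3% (coded 0); false harm in 11.3% (coded 1).
- r = 1: no bias, but the mean standard error of log RR rises from 0.196 to 0.228 (coded 0) or 0.264 (coded 1), because the reference group is smaller.
- Ownership at randomisation recorded and adjusted for in both arms: RR 0.99 to 1.01 and two-sided rejection of about 4% to 6% at every r in the table.

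**The case against.** The strongest reply is that the article never says remote women are not asked about a device of their own. A machine supplied by the trial is not the same thing as prior personal ownership, the case report form is not shown, and an article is a condensed account. This stands as a limit: that ownership is recorded in one arm only is the plain reading, not an explicit statement. But both sentences on the subject define the variable within the control arm. If the data were never collected in the remote arm, a later analysis plan could not supply them.

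It is also fair that the exact model is open. The second sentence could mean restriction or exclusion rather than adjustment. The first, however, does say adjustment. The magnitudes rest on assumed values, and adjusting for chronic hypertension would remove whatever part of the ownership–outcome relation it explains. That stands too.

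Three stronger readings are tempting, and the document does not support them:

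- A reader might infer that the coding alone sets the direction of the bias. It does not: the signs at r = 0.67 are the reverse of those at r = 1.5, and at r = 1 there is no bias.
- A reader might infer that the non-inferiority conclusion is in danger, or that home monitoring among control women is the main threat to it. The primary model does not contain this covariate. The article also places such monitoring within usual care and distinguishes the intervention by transmission of readings to clinicians and immediate interpretation for the patient.
- A reader might infer that control women who monitor at home belong among the per-protocol exclusions. Those are for clear departures from intended care, which this is not under Control arm: usual care. Excluding these women would also bring back a comparison of all remote women with self-selected control women.

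**Conclusion.** The point holds for the sensitivity analysis as described. On the plain reading, the adjusted treatment effect is a non-randomised contrast between the whole remote arm and either control non-owners or control owners. It is biased whenever ownership is related to outcome. With 40% ownership, risk ratios of 0.67 to 1.5 between owners and non-owners shift a null RR to between 0.80 and 1.30, or −7.8 to +7.1 points, against a 15-point margin. With no such relation the only cost is precision.

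These sizes are illustrative. Ownership prevalence and its relation to outcome are assumed, and covariates other than treatment and ownership are left out. The primary intention-to-treat result is untouched. The change is worth making because a stated check would otherwise be hard to interpret and the correction is cheap.

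**What to change.** 1. Record ownership and use of a home blood pressure machine before randomisation, with the same question in both arms.
2. In the sensitivity analysis, adjust for that baseline variable, or report the treatment effect in baseline owners and non-owners with an interaction estimate and its interval, or do both.
3. Drop the word confounder, and state when and in which arms ownership is recorded.
4. Report home monitoring that control women start after randomisation descriptively. Do not treat it as a per-protocol deviation while the article places it within conventional care.

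The cost is one question on the form and revised wording. Trial status says recruitment began in July 2022, so women already enrolled would need a retrospective query. Their answers would come after unblinded allocation and are open to recall error, so they should be flagged as retrospective in the data and in the report. If remote-arm ownership cannot be recovered, the adjustment should be dropped rather than run with a constant value for that arm.

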### Design and setting

The REMOTE Control trial will recruit patients across 3 metropolitan Australian teaching hospitals; Liverpool, Campbelltown and Bankstown Hospitals. Within these hospitals, women at high risk of developing a hypertensive disorder of pregnancy are referred to specialist obstetric medicine clinics, where their blood pressure is monitored regularly throughout their pregnancy, leading to an additional 6–8 clinic reviews. The non-inferiority trial will compare remote blood pressure monitoring with conventional clinic monitoring in a 1:1 allocation ratio.

The trial has been prospectively registered with the Australian and New Zealand Clinical Trials Registry (ACTRN12620001049965p) in October 2020. Ethics approval was granted by the South Western Sydney Local Health District human research ethics committee (SWSLHD HREC) in June 2021.

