### Study population

The study population will be all pregnant women at high risk for developing a hypertensive disorder of pregnancy, that attend the hospital sites for antenatal care. Eligible women must be ≥ 18 years old with at least one of the following high risk features: (1) chronic hypertension; (2) autoimmune disease; (3) pre-existing diabetes mellitus; (4) chronic kidney disease; (5) previous hypertensive disorder of pregnancy; (6) diagnosed with gestational hypertension; (7) IVF pregnancy; or (8) women whose risk of developing early-onset preeclampsia on first-trimester screening is reported to be < 1:100 [38]. Exclusion criteria for participation in the study are (1) evidence of preeclampsia on initial evaluation; (2) inability to access or use a smartphone as assessed by the research midwife on screening and consent; (3) inability to consent or (4) insufficient knowledge of English or other language supported by the application; (5) multiple pregnancy; and (6) lethal foetal abnormalities. The full inclusion criteria, exclusion criteria and definitions are listed in Table 1.

**Table 1 Tab1:** REMOTE CONTROL trial inclusion and exclusion criteria

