	**Definition**
**Inclusion criteria**	
Age ≥ 18 years	
Able to provide informed consent	
Able and willing to follow instructions for use of automated BP machine and app-based system	
Chronic kidney disease	Abnormalities of kidney structure or function (either reduced GFR < 90 ml/min/1.73 m^2^, albuminuria or proteinuria) present prior to pregnancy
Autoimmune disorder	Diagnosis of an autoimmune condition such as systematic lupus erythematosus prior to pregnancy
Type 1 or type 2 diabetes mellitus	
Chronic hypertension	Systolic BP > 140 mmHg or diastolic BP > 90 mmHg on at least 2 occasions prior to 20 weeks’ gestation
Previous pregnancy complicated by HDP or diagnosis of gestational hypertension this pregnancy	Previous HDP includes chronic hypertension, gestational hypertension, preeclampsia, or preeclampsia superimposed on chronic hypertension Gestational hypertension (Systolic BP > 140 mmHg or diastolic BP > 90 mmHg on at least 2 occasions after 20 weeks’ gestation)
Confirmation of viable intrauterine pregnancy on dating scan	
IVF pregnancy	
High-risk for developing preeclampsia on first-trimester screening	Reported risk of < 1:100 of developing preeclampsia on commercially available combined first-trimester screening tests
Before 28 weeks gestation	

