**Exclusion criteria**	
Participants who have signs of preeclampsia on initial evaluation	Preeclampsia (BP reading > 140 mmHg and/or 90 mmHg on at least 2 occasions after 20 weeks’ gestation accompanied by evidence of end-organ involvement)
Multifoetal pregnancy	
Lethal foetal abnormality	Lethal foetal chromosomal, genetic or morphological abnormality detected on screening tests
Inability to access or use the app-based system	
Unable to consent	
Non-English speaking background not supported by the mobile application	

*GFR* glomerular filtration rate, *SLE* systemic lupus erythematosus, *BP* blood pressure, *HDP* hypertensive disorder of pregnancy

Participants will be recruited through both the antenatal and specialist obstetric medicine clinics. Eligible patients will undertake full informed written consent with an Obstetric Physician or research midwife. Consented participants will be randomised in a 1:1 ratio, to receive either conventional care with face-to-face consultations or remote BP monitoring. Computer-generated randomisation will occur through RedCAP™, and a minimisation protocol for the variables chronic hypertension, centre of treatment and aspirin use will be instituted. Individual patient randomisation will be used so that treatment allocation remains unpredictable. To avoid bias, the random allocation sequence is concealed from those responsible for recruiting women into the study, and generated by the REDCap randomisation module. A research midwife based at each site will be responsible for consenting and assigning participants to the trial arms. Blinding of the treatment allocation to the patient and treating physician will be difficult and unethical. Outcome assessors and data analysts will not be blinded to treatment allocation. An overview of the study procedures is shown in Fig. 1.

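### Centre is a minimisation factor but, on the natural reading, is missing from the primary model; the effect is small and conservative, and hypertension type is mislabelled as a minimisation factor

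*Protocol article*

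**What the plan says.** Three statements in the protocol article bear on this.

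- **Randomisation** (Study population, the paragraph after Table 1): "a minimisation protocol for the variables chronic hypertension, centre of treatment and aspirin use will be instituted". That is three factors. Allocation is 1:1, and Design and setting gives three hospitals.
- **Primary model** (Data handling, analysis and result reporting): a generalised linear model with binomial distribution and log link, "adjusting for minimisation variables, chronic hypertension and aspirin use". Binary secondary outcomes follow the same method.
- **Subgroups** (same section): the first set is described as "variables used in the minimisation algorithm (i.e. hypertension type [chronic or gestational hypertension] and LDA use".

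On eligibility, Study population says "Eligible women must be ≥ 18 years old with at least one of the following high risk features". The eight features include autoimmune disease, pre-existing diabetes, kidney disease, IVF and first-trimester screening risk, none of which requires hypertension. Table 1 separates the two hypertension types by gestation: chronic is "Systolic BP > 140 mmHg or diastolic BP > 90 mmHg on at least 2 occasions prior to 20 weeks’ gestation", while gestational needs raised readings after 20 weeks. Entry is before 28 weeks.

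**The concern.** Minimising on a prognostic factor makes the arms more alike on it than simple randomisation would. The treatment comparison is then more precise than a model without that factor recognises, so the reported standard error is too large and the test too cautious. Centre could plausibly matter here, because the composite includes neonatal intensive care or special care nursery admission, which can depend on local practice.

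There is also a question of specification. The covariates of the primary model should be fixed before the data are seen. The article says that data analysts will not be blinded, so wording that can be read with or without centre leaves a choice open that should be closed.

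The subgroup sentence raises a separate, smaller issue. Chronic versus gestational is not the same partition as chronic hypertension present or absent, and a woman enrolled for, say, IVF or diabetes alone may belong to neither group.

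**Working it through.** **1. Comparing the lists.**

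| Place | Chronic hypertension | Aspirin | Centre |
|---|---|---|---|
| Minimisation (Study population) | yes | yes | yes |
| Primary model (Data handling) | yes | yes | not named |
| Minimisation variables as listed for subgroups (Data handling) | replaced by chronic-or-gestational type | yes | not named |

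Centre is absent from both analysis lists.

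**2. The plan's own sample size.** Inputs from the Sample size section: risk p = 0.311 in both arms, margin 0.15, one-sided alpha 0.05, power 0.80.

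n per arm = (z₀.₉₅ + z₀.₈₀)² × 2p(1−p) / margin² = 6.1826 × 2 × 0.214279 / 0.0225 = 117.8, so 118. The stated figure is reproduced. It does not depend on the covariate list, so adding centre changes no stated number.

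At 118 per arm, SE = √(2 × 0.214279 / 118) = 0.0603, and power = Φ(0.15/0.0603 − 1.645) = 0.801.

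**3. Size of the effect of omitting centre.** The documents give no centre-specific risks, so assume three equal-sized centres with risks p − s, p and p + s.

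- Between-centre variance: B = 2s²/3.
- True variance over model variance: R = 1 − B / [p(1−p)].
- SE overstated by 1/√R − 1.
- Actual one-sided alpha = P(Z > 1.645/√R).
- Power without centre = Φ[(0.15/SE − 1.645)/√R].
- Power with centre = Φ[0.15/(SE√R) − 1.645].

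Example, s = 0.10: B = 0.00667, R = 1 − 0.00667/0.214279 = 0.969, √R = 0.984.

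| Assumed centre risks | R | SE overstated | Actual alpha | Power without centre | Power with centre |
|---|---|---|---|---|---|
| 31.1% ± 5 | 0.992 | 0.4% | 0.049 | 0.802 | 0.803 |
| 31.1% ± 10 | 0.969 | 1.6% | 0.047 | 0.804 | 0.812 |
| 20 / 31 / 42% | 0.962 | 1.9% | 0.047 | 0.806 | 0.815 |
| 31.1% ± 15 | 0.930 | 3.7% | 0.044 | 0.809 | 0.825 |
| 15 / 31 / 47% | 0.920 | 4.2% | 0.043 | 0.811 | 0.829 |

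The power forgone runs from about 0.2 to about 2 points. In every row the power without centre remains at or above 0.80.

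**4. The subgroup factor.** The factor minimised was chronic hypertension. The subgroup contrast is chronic against gestational. Because one non-hypertensive feature is enough for entry, the contrast has no stated place for women with neither type. Gestational hypertension also requires readings after 20 weeks and entry closes at 28, so at randomisation it can apply only to later enrolments. The sentence ties antihypertensive therapy, gestational diabetes and smoking to randomisation, but not hypertension type.

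**The case against.** **Ambiguity.** The covariate phrase can be read as a list whose first item, the minimisation variables, already contains centre. This is possible but is the weaker reading: it would count chronic hypertension and aspirin twice, and the subgroup sentence, introduced by *i.e.*, omits centre as well. Centre may have been left out there simply because a three-hospital subgroup is of little interest, so that sentence is supporting evidence and not proof. On either reading the covariates need to be named.

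**Size.** A reader might infer that the omission leaves the trial underpowered or threatens the non-inferiority conclusion. The documents do not support that. The error is conservative and does not bias the estimate, and omission only forgoes a gain above the planned power. The wider spreads in the table are also large for three metropolitan hospitals that the Discussion places in one local health district. This objection stands.

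**Scale.** The calculation uses a risk difference against the 15-point margin at one-sided 0.05, whereas the planned model gives a risk ratio with a 95% interval. That stands too: the figures show the order of magnitude and are not operating characteristics of the planned model.

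**Cost.** Log-binomial models can fail to converge as terms are added, and some binary secondary outcomes, such as neonatal seizures, are likely to be rare. Adding centre is therefore cheap but not entirely free.

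**Subgroup.** A reader might infer that women with neither hypertension type are discarded. The article does not say so, and a third category is compatible with its text. Nothing obliges a subgroup to match a minimisation factor, and these subgroups are limited to the primary outcome and declared hypothesis-generating. What remains is a mislabelled factor and an unstated category.

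**Unseen documents.** Coding detail may sit in the full protocol or SAP. But the article does state these lists, and they disagree with its own randomisation section.

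**Conclusion.** The point holds as a discrepancy in the specification with a small statistical consequence. The article randomises on three factors and, as most naturally read, adjusts for two. Omitting centre would inflate the standard error by about 0.4% to 4%, lower the actual one-sided alpha to about 0.049 to 0.043, and forgo about 0.2 to 2 points of power.

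These figures assume equal-sized centres, centre risks differing by ±5 to ±16 points, 118 evaluable women per arm and a risk-difference approximation; the centre differences are not taken from the documents. The reason to act is that the primary model's covariates should be unambiguous and match the randomisation, not that the result is at risk.

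The subgroup issue is secondary: hypertension type is wrongly called a minimisation variable, and women with neither type have no stated category.

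**What to change.** In Data handling, analysis and result reporting, replace the covariate phrase for the primary and binary secondary outcomes with: *adjusting for all minimisation variables: chronic hypertension (yes/no), aspirin use and centre (3 levels)*. If centre is left out on purpose, say so and give the reason. State in advance what will be done if the log-binomial model does not converge, since that is the main downside for rare secondary outcomes.

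For the subgroup, do one of two things:

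- define it as chronic hypertension yes versus no at randomisation, which matches the factor minimised; or
- keep hypertension type, move it to the other prognostic variables, fix it at randomisation, and add a category for women with neither type.

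The cost is a line or two of wording and two extra model parameters. The sample size does not change.
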